### Relevance and importance of the proposed study: preliminary results of DFCI studies

TE is a significant problem in children receiving therapy on DFCI ALL protocols. Pilot data from Canadian institutions showed 11% prevalence of symptomatic TE in children receiving therapy on DFCI ALL protocols [51]. Older age (≥ 10-years) and high-risk (HR) disease are important risk factors for development of TE; older patients (≥ 10-years) compared to younger patients (44% vs. 4%, *p* < 0.0001) and patients with HR ALL compared to standard-risk (SR) ALL (26% vs. 2%) had higher prevalence of TE (*n* = 91) [51].

The effect of older age and HR ALL on the risk of symptomatic TE was confirmed in Consortium-wide review of earlier protocols; overall incidence of TE in children ≥10 years was 12% compared to 2% in children <10 years of age (*p* < 0.0001) [DFCI ALL studies 91–01 and 95–01 (*n* = 906)] and in children with HR ALL was 17% compared to 1.5% in children with SR ALL (*p* = 0.005) [DFCI 20–01(*n* = 118)]. Of note, data on TE was not consistently collected on earlier DFCI protocols.

The etiology of the increased susceptibility of older and HR ALL patients to TE is unknown, it is likely related to the therapy they receive. Majority of the episodes of TE in patients treated on DFCI ALL therapy protocols occurred during Consolidation phase where ASP and steroids are given concomitantly. Moreover during this phase, HR patients (including all patients ≥10 years) receive thrice as much steroids as SR patients [52]. Compared to the contemporary therapy protocols, DFCI ALL protocols use higher cumulative doses of steroids and ASP.

In contrast to BFM studies, our data showed that the dose, but not the type, of steroid used with ASP significantly altered the risk of TE on DFCI ALL-protocols. Patients receiving high-dose steroids were at significantly higher risk of TE (18.2% Vs 2.7% in patients with lower dose steroids; *p* = 0.004) [53, 54].

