#### Methods for analysis

Patient demographics, prognostic characteristics and clinical outcome will be summarized using descriptive measures expressed as mean (standard deviation) or median (minimum, maximum) for continuous variables and number (percent) for categorical variables. The analysis will adopt the intention-to-treat principle. Since TE is a safety outcome for ALL-therapy we will also perform “per-protocol” analysis. Association between categorical outcomes and groups will be assessed using Fisher’s Exact test or chi-squared test. Thrombosis-free survival will be estimated using Kaplan-Meier method. The limit for statistical significance will be set at α = 0.05. In all comparison, 95% confidence intervals (CI) of the measure of association between groups will be reported.

Logistic regression will be used to analyze data for both primary and secondary outcomes. Analysis results of regression modeling will expressed as coefficient, corresponding standard error, 95% CI and associated *p*-values. Variance inflation factors will be used to assess multi-colinearity among predictors. Model assumptions will be assessed through residual analysis. Goodness-of-fit will be evaluated using qq plots for normality and coefficient of determination and R^2^ for regression models. Some of the time dependent confounding variables like infection or CVL-related problems (which may influence the risk of TE) are unpredictable and hence cannot be adjusted prospectively. To compensate for that we will prospectively collect the information and enter in the regression model when risk factors for thrombosis are being analyzed. All analyses will be performed using SPSS 14 software (2005 SPSS Inc). Table 3 provides a summary of specific methods of analysis for primary and secondary outcomes.

**Table 3 Tab3:** Proposed Methods of Analysis

Analysis	Hypothesis	Independent variable	Outcome variable		Method of analysis
			Name	Variable type	
Primary	Presence of one or more prothrombotic defect/s increase the risk of TE	Presence of one or more prothrombotic defect	Symptomatic TE	Binary	Fisher’s Exact Test Analysis performed for overall prevalence of at least one prothrombotic defect and for individual defect.
Secondary					
Aim 1.	1.a Older age increases the risk of TE, especially in presence of one or more prothrombotic defect	Age of the patient (age < 10 years, age ≥ 10 years)	Symptomatic TE	Binary	Logistic regression

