	1.b HR/VHR ALL increases the risk of TE, especially in presence of one or more prothrombotic defect	Risk categorization of ALL (HR/VHR ALL, SR ALL)			
	1.c PEG ASP therapy increases the risk of TE, especially in presence of one or more prothrombotic defect	Type of ASP (*E. coli* ASP, PEG ASP)			
Aim 2	A mathematical model can be used to determine the risk of symptomatic TE	Clinical Variables: age of the patient, risk categorization of ALL presence or absence of prothrombotic defect, Therapy variable: type of ASP used	Symptomatic TE	Binary	Regression analysis will be used to predict the risk of TE
Aim 3	The overall (presence of at least one tested) prevalence of one or more prothrombotic defect is at least 20%		Prevalence of one or more prothrombotic defect/s	Categorical	Prevalence of individual and overall prothrombotic defect will be expressed as percentage of affected patients with 95% CI

Logistic regression will be used to analyze the data for both primary and secondary outcomes. Analysis results of regression modeling will be expressed as coefficient, corresponding standard error, 95% CI and associated *p*-values. Variance inflation factors will be used to assess multi-collinearity among predictors. Missing values will be handled using multiple imputation or last observation carried forward. Model assumptions will be assessed through residual analysis. Goodness-of-fit will be evaluated using qq plots for normality and coefficient of determination and R2 for regression models

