#### Sample size

The sample size calculation is based around the primary aim of the study. The null hypothesis for the primary aim of this study that there is no difference in the proportion of patients developing TE with or without prothrombotic defect. The criterion for significance is set at two sided α = 0.05. *Minimal clinically important difference (MCID):* The purpose of this study is to identify a population at high risk for TE, so that we can develop strategies for prevention of TE. The MCID we wish to detect will be guided by the numbers needed to treat (NNT) to prevent one event of TE. If we have to use presence of prothrombotic defect as the only criteria for effective thromboprophylaxis, we aim to detect a MCID of at least 25%. This will mean that, we will need to treat ~4 patients to prevent one event of TE. Table 4 outlines the required sample size calculation and NNT at various levels of MCID. Based on the preliminary data from Canadian institutions on previous DFCI protocol 20–01, the incidence of TE is estimated to be 11%. Based on previous studies, the overall prevalence of prothrombotic defect (presence of at least one prothrombotic defect) in the study cohort is estimated to be 20% [38, 39, 48]. With a sample of 150 patients (30 patients with and 120 without prothrombotic defect) there is more than 80% chance of detecting MCID of 25% at a two-sided significance level of 0.05.

**Table 4 Tab4:** Sample size calculation requirements to compare cumulative TE in patients with and without prothrombotic defects

δ	Sample size for each group	Estimated sample size for proposed study (α =0.05 and β = 0.2, with 20% prevalence of prothombotic defects based on previous studies [12])			Number of patients needed to treat to prevent one event of TE (NNT)
		With PD	Without PD	Total	
0.40	16	16	80	96	approximately 3 patients
0.30^a^	24	24	120	144	approximately 4 patients
0.20	41	41	205	246	5 patients
0.10	102	102	510	612	10 patients

^δ^Difference in the cumulative incidence of TE in patients with and without prothrombotic defects

^a^Minimal clinically important difference

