#### Feasibility

At three participating institutions, every year about 90 children are diagnosed with ALL. Our experience on previous protocols indicate almost 100% patient participation in DFCI ALL studies. However, accounting for ineligibility or non-enrollment either on DFCI 05–01 study (~5%) or the proposed thrombophilia study (~5%) and withdrawal from DFCI 05–01 study (~5%) we anticipate a sample size of at least 150 patients over the period of 2 years. Based on the previous experience of age distribution and risk-stratification, we anticipate that about 26 patients will be 10 years or older and ~80 patients will be classified as HR/VHR ALL in the study cohort of 150 patients. With 17% incidence of TE in HR population and about 2% in SR population based on our previous analysis, we anticipate about 14 patients with TE in HR/VHR group and 2 patients with TE in the SR group. All three centers have the necessary laboratory and technical support for investigational blood collection. Hence, the proposed study is feasible to address the primary aim.

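### The logistic models for Secondary Aims 1 and 2 are checked with linear-regression tools, and the risk-group-by-defect question rests on about two standard-risk events

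*Protocol article*

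**What the plan says.** All references are to the protocol article.

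- **Models.** Methods for analysis and Table 3 plan logistic regression of symptomatic TE, labelled binary, for Secondary Aim 1. Hypothesis 1.a concerns age (under 10 versus 10 or over), 1.b risk group and 1.c asparaginase type. Aim 2 is a prediction model whose predictors are "Clinical Variables: age of the patient, risk categorization of ALL presence or absence of prothrombotic defect, Therapy variable: type of ASP used".
- **Effect modification.** Hypothesis 1.b reads: "HR/VHR ALL increases the risk of TE, especially in presence of one or more prothrombotic defect". Hypotheses 1.a and 1.c have the same form. The preliminary-results section says the study will evaluate the interaction of defects with age, risk category and asparaginase type. The Hypotheses section speaks of these factors alone or combined with a defect.
- **Fit checks.** "Goodness-of-fit will be evaluated using qq plots for normality", together with the coefficient of determination and R-squared. This is stated in the text and repeated under Table 3. Residual analysis and variance inflation factors are also named.
- **Age and risk group.** The preliminary-results section says "HR patients (including all patients ≥10 years) receive thrice as much steroids as SR patients".
- **Expected events.** Feasibility says "we anticipate about 14 patients with TE in HR/VHR group and 2 patients with TE in the SR group", from about 80 high-risk or very-high-risk (HR/VHR) patients in a cohort of 150.

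**The concern.** Three features of the secondary analyses do not fit the data the plan expects.

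1. **Fit checks.** The named tools belong to linear regression. Residuals of a 0/1 outcome are not normal, so a normal QQ plot carries no information about whether a logistic model fits. R-squared says nothing about calibration. A small-sample prediction model needs checks on calibration and on optimism, meaning apparent discrimination above what new patients would show. The named tools give neither.
2. **Risk group by defect.** To estimate how a defect changes the effect of HR/VHR disease, there must be events among standard-risk (SR) children both with and without a defect. The plan expects about two SR events in all.
3. **Age tested alone.** If every child aged 10 or over is HR, hypothesis 1.a on its own compares an all-HR group with a mixture of SR and HR children. Part of any age effect is then the risk-group effect.

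The study is meant to identify children at high risk of TE and to inform a later prophylaxis trial. An overconfident risk model, or an interaction odds ratio that is infinite for lack of events, would be a poor basis for either.

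**Working it through.** **Inputs.** 150 patients, 20% with a defect and 11% TE (Sample size). 80 HR/VHR, hence 70 SR; 26 aged 10 or over; TE 17% in HR and about 2% in SR (Feasibility). Update: 131 patients, 15% TE (Study progress).

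**Reproducing the plan's event counts.** 80 × 0.17 = 13.6 (stated 14). 70 × 0.02 = 1.4 (stated 2). Overall, 14 + 2 = 16, against 150 × 0.11 = 16.5.

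**Events per term, Aim 2.** 16 / 4 = 4.0. With the update, 131 × 0.15 = 19.7, about 20, and 20 / 4 = 5.0. Adding ABO group, as Study progress does, gives 16 / 5 = 3.2 or 20 / 5 = 4.0.

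**Empty SR-by-defect cells.** At 20% prevalence the 70 SR children split into 14 with and 56 without a defect. P(at least one cell without an event) = 1 − [1 − (1 − p₁)^14] × [1 − (1 − p₀)^56].

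| SR risk with / without defect | (1 − p₁)^14 | (1 − p₀)^56 | P(empty cell) |
|---|---|---|---|
| 2% / 2% | 0.754 | 0.323 | 0.83 |
| 6% / 1% (average 0.2 × 6 + 0.8 × 1 = 2%) | 0.421 | 0.570 | 0.75 |

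The 6%/1% split is an assumption. An empty cell separates the data along the cell indicator, so the maximum-likelihood interaction estimate is not finite, whatever other covariates are in the model.

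Sensitivity:
- If the SR rate is 2/70 = 2.9%, matching the stated 2 events rather than 1.4, the two rows become 0.73 and 0.60.
- With 131 patients and the same risk mix (131 × 70/150 ≈ 61 SR, an assumption) at 20% prevalence (12 and 49), they become 0.86 and 0.80.
- If prevalence were 50% (an assumption; the article says only that it is high), 61 SR children at 2% in both cells give 0.79.

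**If the cells are not empty.** Take the good case of 2 SR events, one in each cell, and 14 HR events, 5 of them in the 16 HR patients with a defect. The variance of the log interaction odds ratio is 1/5 + 1/11 + 1/9 + 1/55 + 1/1 + 1/13 + 1/1 + 1/55 = 2.515, so SE = 1.59. The 95% interval multiplies and divides the estimate by exp(1.96 × 1.586) = 22.

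**Age and risk group.** The implied table is:

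| | <10 years | ≥10 years |
|---|---|---|
| SR | 70 | 0 |
| HR/VHR | 54 | 26 |

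The correlation is (26 × 70 − 0 × 54) / √(80 × 70 × 26 × 124) = 0.43, and the variance inflation factor is 1 / (1 − 0.43²) = 1.22. Both main effects can therefore be estimated jointly, and the planned collinearity check would raise no flag. In the joint model the age effect comes only from the 80 HR patients and their 14 or so events. If 7 of those events fall in each age group, SE = √(1/7 + 1/19 + 1/7 + 1/47) = 0.60, a 95% interval of about ×/÷ 3.2.

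**Optimism of the Aim 2 model.** In 600 simulated cohorts of 150 per setting, assuming TE of 2%, 12% and 27% in SR, HR under 10 and age 10 or over, a defect odds ratio of 1 or 3, 1:1 asparaginase and 55% non-O, there were 15–19 events on average. The mean apparent c-statistic was 0.79–0.82 and the mean value in new patients 0.74–0.77. The difference was 0.04–0.05 with four terms and 0.05–0.07 with ABO added.

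**The case against.** Several points on the other side are sound.

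- **Nesting is not collinearity.** A reader might infer that age and risk group cannot enter one model, or that they should be recoded as a three-level factor. The documents do not support this. With about 54 HR children under 10, both effects are estimable, and with the SR ≥10 cell empty the three-level factor is the same two-degree-of-freedom model with the same fitted risks. What stands is narrower: hypothesis 1.a tested alone mixes age with risk group. The list of study variables also gives age as continuous, so the cut at 10 is certain for Aim 1 but not for Aim 2.
- **Size of the model.** Adding up blood counts, phase of therapy, ABO group and interactions suggests a model of about 12 terms with severe overfitting. No section puts those terms in one model: Aim 2 lists four and the later amendment adds ABO. Optimism measured with pure-noise predictors would also ignore the strong age and risk-group effects in the preliminary data (12% versus 2% by age, 17% versus 1.5% by risk group). Under effects of that order it is modest.
- **R-squared.** Pseudo-R-squared measures are routine in logistic regression. This is fair, but they do not measure calibration, and the normal QQ plot remains inapplicable.
- **Status.** These are secondary aims under an exploratory objective, Feasibility is claimed only for the primary aim, and an article may leave validation detail to an analysis plan. The omission of such detail is not the point. The article names specific fit tools, twice, and one of them is wrong for the model.

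**Conclusion.** The point holds in a limited form.

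1. The stated goodness-of-fit tools do not suit a logistic model. A normal QQ plot tests nothing in it, and neither that plot nor R-squared would reveal miscalibration or optimism in a model with about 4 to 5 events per listed term. Under the assumed effects the expected optimism in the c-statistic is about 0.04–0.07. That is worth correcting, but it does not show that the model would be useless.
2. The HR/VHR-by-defect question cannot be expected to yield a usable ordinary logistic estimate. At the plan's 2% SR rate and 20% prevalence, the chance of a non-finite interaction odds ratio is 75–83%, and 60–73% if the SR rate is 2/70. The smaller cohort of 131 does not help unless SR events are more frequent than planned; the article gives no updated split by risk group.
3. Hypothesis 1.a tested alone does not isolate age.

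The two-SR-event limit applies directly to risk group by defect. The age-by-defect question has its own limit, about 26 × 0.2 = 5 older children with a defect. The primary Fisher comparison is untouched.

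**What to change.** - Replace the QQ plots and R-squared with a bootstrap optimism-corrected c-statistic, a calibration slope and a calibration plot for the Aim 2 model.
- Keep that model to the four listed baseline terms plus ABO group, and fit it with shrinkage. If Firth's method is used for prediction, correct the intercept, because the plain version tends to raise predicted risks.
- Report the effect of a defect by risk group as TE risks in each stratum with exact confidence intervals, or as Firth or other penalised estimates, instead of ordinary interaction tests.
- Report the age effect within HR/VHR patients or from the model containing both age and risk group, and state that no age effect can be estimated in SR disease.

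**Cost.** Wording in the analysis section and a little more analysis work. No new data are needed, and the article says the study is still in follow-up. Software beyond the named SPSS 14 may be required. The reported discrimination will be somewhat lower than the apparent value, and the effect-modification results will be visibly imprecise.

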#### Sample size

The sample size calculation is based around the primary aim of the study. The null hypothesis for the primary aim of this study that there is no difference in the proportion of patients developing TE with or without prothrombotic defect. The criterion for significance is set at two sided α = 0.05. *Minimal clinically important difference (MCID):* The purpose of this study is to identify a population at high risk for TE, so that we can develop strategies for prevention of TE. The MCID we wish to detect will be guided by the numbers needed to treat (NNT) to prevent one event of TE. If we have to use presence of prothrombotic defect as the only criteria for effective thromboprophylaxis, we aim to detect a MCID of at least 25%. This will mean that, we will need to treat ~4 patients to prevent one event of TE. Table 4 outlines the required sample size calculation and NNT at various levels of MCID. Based on the preliminary data from Canadian institutions on previous DFCI protocol 20–01, the incidence of TE is estimated to be 11%. Based on previous studies, the overall prevalence of prothrombotic defect (presence of at least one prothrombotic defect) in the study cohort is estimated to be 20% [38, 39, 48]. With a sample of 150 patients (30 patients with and 120 without prothrombotic defect) there is more than 80% chance of detecting MCID of 25% at a two-sided significance level of 0.05.

**Table 4 Tab4:** Sample size calculation requirements to compare cumulative TE in patients with and without prothrombotic defects

δ	Sample size for each group	Estimated sample size for proposed study (α =0.05 and β = 0.2, with 20% prevalence of prothombotic defects based on previous studies [12])			Number of patients needed to treat to prevent one event of TE (NNT)
		With PD	Without PD	Total	
0.40	16	16	80	96	approximately 3 patients
0.30^a^	24	24	120	144	approximately 4 patients
0.20	41	41	205	246	5 patients
0.10	102	102	510	612	10 patients

^δ^Difference in the cumulative incidence of TE in patients with and without prothrombotic defects

^a^Minimal clinically important difference

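### Table 4 places an equal-group sample size in the smaller of two unequal groups and still labels the totals beta = 0.2; at the rate that reproduces the table, the printed splits have about 97–98% power

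*Protocol article*

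**What the plan says.** All of this is in the protocol article, Statistical considerations, Sample size.

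- Test level: "The criterion for significance is set at two sided α = 0.05".
- Target: "we aim to detect a MCID of at least 25" percentage points.
- TE rate: "the incidence of TE is estimated to be 11" per cent. The text does not say whether this is also the rate in children without a defect, and it gives no separate rate for either group.
- Prevalence of at least one defect: "in the study cohort is estimated to be 20" per cent.
- Power statement: "With a sample of 150 patients (30 patients with and 120 without prothrombotic defect) there is more than 80% chance of detecting MCID of 25" points.
- Table 4 gives one per-group number for each difference, repeats it under *With PD*, and puts five times that number under *Without PD*. The columns are headed "Estimated sample size for proposed study (α =0.05 and β = 0.2, with 20% prevalence of prothombotic defects". The last row, for a difference of 0.10, reads "102 102 510 612".

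Table 3 names Fisher's exact test for the primary comparison.

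**The concern.** A sample size per group for two equal groups reaches 80% power when the other group is the same size. If the other group is made five times larger and the rates stay the same, power must rise. In the 0.30 row, for example, 24 against 24 and 24 against 120 cannot both have beta = 0.2. Either the per-group column or the totals are mislabelled.

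The section sends the reader to this table for the sample size and number needed to treat at each candidate difference. If the totals are wrong, that trade-off is wrong, and readers are misinformed about what the design can detect. Enrolment was later described as very slow and the target was cut to 131, so the number truly required had practical weight.

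**Working it through.** **Inputs.** Two-sided alpha 0.05 (z = 1.960), beta 0.2 (z = 0.8416), and the differences and group sizes in Table 4. The rate without a defect, p0, is not given in the section. It was found by searching for the value that reproduces the table.

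**Formula.** For a defect group of size n, a comparison group of size kn, p1 = p0 + δ and p̄ = (p1 + k·p0)/(1 + k):

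n = [1.960·√((1 + 1/k)·p̄(1 − p̄)) + 0.8416·√(p1(1 − p1) + p0(1 − p0)/k)]² / δ²

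**Step 1: reproduce the plan's figures (k = 1, p0 = 0.02).** For δ = 0.30, p1 = 0.32 and p̄ = 0.17. The two terms are 1.960 × √0.2822 = 1.041 and 0.8416 × √0.2372 = 0.410. Then (1.451)²/0.09 = 23.4, rounded up to 24.

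| δ | n, equal groups | rounded up | Table 4 |
|---|---|---|---|
| 0.40 | 15.6 | 16 | 16 |
| 0.30 | 23.4 | 24 | 24 |
| 0.20 | 40.2 | 41 | 41 |
| 0.10 | 101.0 | 102 | 102 |

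All four rows match. The same formula gives 29.9, hence 30, at δ = 0.25. The Background cites 2.2% TE in children without a defect in the German study, which is close to the inferred 2%.

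**Step 2: same rate, unequal groups.** For δ = 0.30 and k = 5, p̄ = 0.07. The terms are 1.960 × √0.07812 = 0.548 and 0.8416 × √0.22152 = 0.396. Then (0.944)²/0.09 = 9.9, so 10 + 50 = 60. With k = 4, n = 10.9, so 11 + 44 = 55.

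| δ | printed total | needed at 1:5 | needed at 1:4 | power of printed split, normal / Fisher |
|---|---|---|---|---|
| 0.40 | 96 | 42 | 40 | 97.7% / 98.2% |
| 0.30 | 144 | 60 | 55 | 97.5% / 98.3% |
| 0.20 | 246 | 108 | 100 | 97.2% / 98.3% |
| 0.10 | 612 | 282 | 255 | 96.7% / 97.4% |

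The 1:5 column isolates the allocation error. The 1:4 column also corrects a separate slip: the printed splits hold 16/96 = 16.7% with a defect, not the stated 20%.

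**Step 3: the text's 11%.** A 2% rate does not fit the text. With 20% prevalence and a 25-point difference it implies 0.02 + 0.2 × 0.25 = 7% overall. There are two ways to use 11%:

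- 11% overall: p0 = 0.11 − 0.2δ, which gives 6% against 31% at 25 points and 7% against 27% at 20 points.
- 11% without a defect: 11% against 36% at 25 points and 11% against 31% at 20 points.

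| 30 vs 120 | Fisher power, 25 points | Fisher power, 20 points | detectable at 80% power (normal / Fisher) |
|---|---|---|---|
| 2% without a defect | 97% | 92% | 14.4 / 15.6 points |
| 11% overall | 92% | 79% | 19.6 / 20.4 points |
| 11% without a defect | 85% | 69% | 22.1 / 23.3 points |

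**Step 4: the 0.10 row at 11%.** With 102 against 510, Fisher power is 78% if 11% is the overall rate (9% against 19%) and 72% if it is the rate without a defect (11% against 21%).

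**The case against.** The strongest reply is that the operative sentence is correct. Thirty against 120 does give more than 80% power for 25 points on either reading of 11%, and 85% on the second reading is close to what the sentence says. This stands. A reader who infers from Table 4 that the study is underpowered, or that the power statement is false, goes further than the document allows.

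Three other inferences are tempting and should be resisted.

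- *That 150 patients detect about 20 points while the table demands 246.* This mixes two baselines. The 246 rests on 2%, while about 20 points rests on 11% as overall incidence. If 11% is the rate without a defect, power at 20 points is only 69%.
- *That the totals are too large at any TE rate.* Step 4 shows otherwise: in the 0.10 row beta = 0.2 is roughly right, or optimistic, at 11%.
- *That the table led the sponsor to give up a smaller target.* The text says only that the target was guided by the number needed to treat. Nor would a null result be judged on planned power alone, because Methods for analysis promises 95% confidence intervals for all comparisons.

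It is also fair to say that the 2% is inferred, and that the 30 may simply be 20% of 150, the accrual anticipated under Feasibility. The match at δ = 0.25 therefore does not prove where the 30 came from. Table 4 is different: one rate reproduces all four rows, and the table itself repeats the per-group number beside a group five times larger.

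**Conclusion.** The point holds for Table 4. Its per-group column is an equal-allocation size, its totals describe a 1:5 comparison, and the two cannot share beta = 0.2 at the same rates. At the inferred 2% the printed totals are more than twice what 80% power needs, and true beta is about 0.02–0.03.

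For the chosen target the error is conservative, so the study is not put at risk. The power sentence is true but imprecise. The difference detectable with 80% power in 150 patients is roughly 14 to 23 points, and about 20 only if 11% is the overall incidence. The underlying gap is that the section never states the TE rate in each group, and the rate that generates the table disagrees with the 11% in the text. This is a correction worth making to a table the plan relies on, not a flaw in the design's adequacy.

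**What to change.** 1. Recompute *With PD*, *Without PD* and *Total* in Table 4 with the unequal-allocation formula, or with exact Fisher power to match the primary test, at the stated 20% prevalence (1:4).
2. Print the assumed TE rate in each group for every row, and make it consistent with 11%, saying whether 11% is the overall rate or the rate without a defect.
3. Restate the power of 30 against 120 with its assumption: for 25 points, about 92% if 11% is overall and about 85% if it is the rate without a defect.
4. If power is reported for the revised 131 patients, use the observed incidence and prevalence. Study progress bases that reduction on 15% incidence and a high prevalence of defects, so a figure at 20% prevalence would not describe it.

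While the table is open, reconcile its footnote, which marks 0.30 as the target difference, with the 25 points in the text.

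The cost is one recomputed table and a reworded sentence. Patients, data and the analysis are unaffected.
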